## Abstract

**Background:**

A large number of randomized trials on the use of acupuncture to treat chronic pain have been conducted. However, there is considerable controversy regarding the effectiveness of acupuncture. We designed a randomized trial involving patients with chronic neck pain (CNP) to investigate whether acupuncture is more effective than a placebo in treating CNP.

**Methods/design:**

A five-arm, parallel, single-blinded, randomized, sham-controlled trial was designed. Patients with CNP of more than 3 months’ duration are being recruited from Guangdong Provincial Hospital of Chinese Medicine (China). Following examination, 175 patients will be randomized into one of five groups (35 patients in each group) as follows: a traditional acupuncture group (group A), a shallow-puncture group (group B), a non-acupoint acupuncture group (group C), a non-acupoint shallow-puncture group (group D) and a sham-puncture group (group E). The interventions will last for 20 min and will be carried out twice a week for 5 weeks. The primary outcome will be evaluated by changes in the Northwick Park Neck Pain Questionnaire (NPQ). Secondary outcomes will be measured by the pain threshold, the Short Form McGill Pain Questionnaire-2 (SF-MPQ-2), the 36-Item Short-Form Health Survey (SF-36) and diary entries. Analysis of the data will be performed at baseline, at the end of the intervention and at 3 months’ follow-up. The safety of acupuncture will be evaluated at each treatment period.

**Discussion:**

The purpose of this trial is to determine whether traditional acupuncture is more effective for chronic pain relief than sham acupuncture in adults with CNP, and to determine which type of sham acupuncture is the optimal control for clinical trials.

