## Background

Chronic neck pain (CNP) is a serious public health and socioeconomic problem worldwide. Studies have shown that the overall prevalence of CNP varies from 0.4 to 86.8% (mean 23.1%) [1]. The prevalence of CNP is greater among office workers than manual workers. This condition is characterized by activity limitations, dizziness, anxiety and insomnia [2]. Physical exercise, massage or physiotherapy, as well as education, have been proved to be efficient in reducing neck pain [3–6]. Acupuncture has also been well accepted as a non-pharmacological treatment for neck pain [7]. However, the treatment effect of acupuncture is moderate [8]. One argument is that “acupuncture is not associated with clinical effects beyond a powerful placebo response” [9, 10].

A growing body of research indicates that clinical trials of acupuncture have encountered many methodological challenges, including the identification of appropriate treatment and control groups, deficiencies in the blinding and follow-up of chronic pain [11]. Firstly, variable acupoints at different sites are commonly selected for the same disease in clinical practice. Based on our clinical experience, more than 20 acupoints have been selected as the main acupoints in neck pain. An appropriate repeatable treatment has not been established. Secondly, although shallow needle insertion and non-acupoints have been widely used in acupuncture research in sham groups, it has been suggested that these methods have therapeutic effects and are adjusted to accommodate different patients according to traditional Chinese medicine (TCM) theory [12]. The academic literature also indicates that the human body has more than 2200 singular points within formal naming beyond meridians [12]. The notion of a non-acupoint is obscure and there may be a role for specific factors of non-acupoints lateral to the acupoints [13]. Moreover, recent academic literature has shown that shallow puncture also produces analgesic effects in pain disorders. Thirdly, it has been reported that about 40% of subjects in these trials could distinguish non-penetrating sham acupuncture from real acupuncture [14].

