In view of these doubts, the influence of different needling points and depths should be investigated. First, the acupoints of local lesions including *Jingbailao* (EX-HN 15) and *Jianzhongshu* (SI 15) are commonly used in our hospital for neck pain [15]. The analgesic mechanism of acupoints on local lesions has been established in the spinal segments control theory to explain the gate control theory [16, 17]. According to the innervations of the pain focus, the effects of stimulation of EX-HN 15 and SI 15 on neck analgesia will be studied for feasibility and repeatability [15]. Second, several different groups of non-acupoints and shallow punctures will be established to determine whether traditional acupuncture is more effective for chronic pain relief than sham acupuncture in adults with CNP. The different depth and placement of needle insertion will also be investigated to determine efficacy [18]. Third, a single-blinded practice will be used and the adequacy of subject blinding will also be carefully assessed. The patients will be advised to lie in the prone position on the treatment couch and will be unaware of the treatment course in this trial. Data collection will be completed by the researchers over a 3-month follow-up period. Finally, we will assess the pain threshold (PT) and pain diary as semi-objective outcomes to avoid subjective results.

In this research, a randomized clinical trial will be performed to determine whether the outcome of traditional acupuncture treatment is significantly different to sham acupuncture in relieving CNP. We also aim to investigate which type of sham acupuncture is the optimal control for clinical trials.

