#### Sample size calculation

Following an academic literature review, a pilot study on acupuncture and its analgesic effect in CNP was identified [26]. The NPQ will be used as the primary outcome measure in assessment of the analgesic effect of acupuncture in this trial. Results from the pilot study with a two-arm design showed that the mean changes in NPQ were 20.71 ± 11.91 (acupuncture group) and 24.04 ± 11.83 (control group) [26]. However, our trial is a five-arm parallel-group study with the aim of assessing the efficacy of acupuncture. The mean ± standard deviation (SD) values reported in the pilot study will be used as the expected values in the treatment group and four control groups in the present study. PEMS 3.1 software was used to perform the sample size calculation. Thus, we calculated the appropriate trial sample size with 90% power, and the significance level was 0.05. The results showed that a clinically important difference was detected using a minimum sample size of 30 individuals in each group. With a maximum allowable dropout rate of 15%, a total of 175 subjects (35 per group) are being recruited.

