#### Statistical analysis

A statistical analysis will be performed using the Statistical Package for Social Sciences (SPSS, version 16.0, SPSS Inc., Chicago, IL, USA) in the Center of Acupuncture Clinical Research. A full analysis set (FAS) will be performed as the main analysis. According to the principle of intention-to-treat (ITT), any participants who randomly receive at least one treatment should be included in the main analysis dataset. The per-protocol (PP) set as the subset of FAS will include subjects who complete the study and have main variable baseline values in this trial. To be included in the safety set, patients will receive at least one safety evaluation after treatment. Statistical analysis of the main parameters will be carried out at baseline, at each visit and in the follow-up period. Frequency tables and charts will be used to analyze completed AE questionnaires.

Descriptive statistics will be performed to compare baseline information, patient characteristics and an evaluation of the credibility of the five groups. To determine the primary and secondary outcomes, the mean differences from baseline to the end of follow-up period will be compared and analyzed. Group differences for continuous variables will be analyzed using analysis of variance (ANOVA) to compare the subjective and semi-objective outcomes. The Wilcoxon rank sum test will be used to compare the outcome measurements before and after treatment. The differences in categorical variables between groups and adverse effects will be analyzed using the chi-square test. A *P* value of 0.05 or less will be considered significant.

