Clinical trials of traditional acupuncture for chronic pain, with optimal control groups, are rare, with the exception of the use of standard outcome measures and rigorous blinding of participants to treatment assignment [38]. However, few guidelines exist for conducting appropriate sham acupuncture, for the depth of the inserted needle or the parameter for needle stimulus [39, 40]. This randomized placebo-controlled trial addresses the urgent need to provide evidence-based control groups for adults with CNP and to determine the evidence for the specificity of acupoints. At the end of this clinical trial, we expect that the findings will provide evidence to answer the question: is acupuncture more effective than a placebo?

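### The trial is to determine the optimal sham control, but optimal is undefined, and difference tests with 30 to 35 patients per arm cannot show that a sham lacks activity of its own

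*Protocol article*

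**What the plan says.** The Discussion paragraph of the abstract names two purposes: to test traditional acupuncture against sham, and "to determine which type of sham acupuncture is the optimal control for clinical trials". The Background repeats the second in softer terms: "We also aim to investigate which type of sham acupuncture is the optimal control for clinical trials". The main Discussion adds the aim "to determine the evidence for the specificity of acupoints". None of these places defines optimal.

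The protocol gives two reasons to doubt existing shams. One is activity: of shallow and non-acupoint needling, the Background notes that "it has been suggested that these methods have therapeutic effects", and the Discussion returns to this. The other is blinding: both sections report that a large share of patients could tell the non-penetrating needle from real treatment.

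For efficacy, the Statistical analysis section names ANOVA between groups, a Wilcoxon test for before versus after, and chi-square tests for categorical data. Its threshold is that a P "value of 0.05 or less will be considered significant". It gives no margin. On the blinding side, the Blinding section plans questionnaires at three time points and a Blinding Index, and Statistical analysis plans to compare the credibility of the arms. Neither is tied to the choice of a sham.

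Sample size calculation gives all four control arms the same expected NPQ change and arrives at 30 evaluable and 35 randomized patients per arm.

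**The concern.** If part of the worry about shams is that they relieve pain themselves, then part of the case for a good sham is that it has no relevant effect beyond the non-penetrating needle (group E), the only arm in which the skin is not pierced. That is a statement of no relevant difference. A difference test cannot establish it, because a non-significant result may mean either no effect or too few patients.

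The size was not set for this question either. With one expected value for all four controls, the calculation neither separates the shams nor shows them alike.

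At stake is the recommendation to later trials. A sham with real activity could be taken up as a neutral control because the arms were small, and later trials that used it would understate the effect of acupuncture. Adding pairwise tests at 0.05 would not cure this, since their non-significant results would be open to the same misreading.

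**Working it through.** **Inputs.** From Sample size calculation: "the mean changes in NPQ were 20.71 ± 11.91 (acupuncture group) and 24.04 ± 11.83 (control group"), so the difference is 24.04 − 20.71 = 3.33 points and the pooled SD is √((11.91² + 11.83²)/2) = 11.87. Also from there: "we calculated the appropriate trial sample size with 90% power", and "the significance level was 0.05" (two-sided is assumed, because the protocol does not say). Arm size is n = 30 evaluable to 35 randomized.

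**The plan's own figure.** Two-group formula: n = 2 × ((1.96 + 1.282) × 11.87 / 3.33)² ≈ 267, or 268 per arm with the reference routine. A five-arm ANOVA with means 20.71 and four times 24.04 needs 246 per arm. The stated 30 is not reproduced. It would fit a difference of (1.96 + 1.282) × 11.87 × √(2/30) ≈ 9.9 points. So the arms are small even for the stated planning difference.

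**Precision of one sham contrast.** SE = 11.87 × √(2/n), which is 3.06 at n = 30 and 2.84 at n = 35. With the variance pooled over five arms (df = 5n − 5), the 90% CI half-width is 5.07 and 4.69 points. The 95% half-width is about 6.0 and 5.6 points, wider than 3.33.

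**Chance that a real difference gives P > 0.05.** For a true difference δ this is approximately Φ(1.96 − δ/SE), computed with the noncentral t, pooled variance and no multiplicity adjustment:

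| True difference | n = 30 | n = 35 |
|---|---|---|
| 3.33 points (protocol) | 81% | 79% |
| 5.94 points (0.5 SD, assumed) | 51% | 45% |
| 8 points (assumed) | 26% | 20% |
| 10 points (assumed) | 10% | 6% |

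**The same check with the test the plan names.** If one arm differs from the other four by 3.33 points, the five-arm ANOVA has power 0.160 and 0.182, so it is non-significant 84% and 82% of the time. If one arm differs by 0.5 SD, power is 0.456 and 0.527, so it is non-significant 54% and 47% of the time. The result does not depend on choosing pairwise tests. Adjusting pairwise tests for all 10 pairs (level 0.005) raises the miss rate at 0.5 SD to 81% and 76%.

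**What an equivalence test could show.** With two one-sided tests at 0.05 and a true difference of zero, power is approximately 2Φ(margin/SE − 1.645) − 1, or zero if that is negative:

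| Assumed margin | n = 30 | n = 35 |
|---|---|---|
| 3.33 points | 0% | 0% |
| 6 points | 25% | 36% |
| 8 points | 67% | 76% |
| 10 points | 89% | 94% |

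A 3.33-point margin would need about 276 patients per arm for 90% power.

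**The case against.** The strongest reply is that the protocol contains no such rule. It never says that P above 0.05 will be read as inert, or that shams will be ranked by which comparison with traditional acupuncture is significant. It does not equate optimal with inert either. The best control could be the best-blinded one, and for that the protocol plans a Blinding Index and a comparison of credibility. Contrasts and margins for a second aim are also often left to an analysis plan, which is not shown here. All of this stands, and it limits the point.

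A reader might go further and infer that the second aim is an equivalence claim, that the P value is the only yardstick, or that an active sham will look inert about half the time. The documents do not support these. The first needs a definition that the protocol does not give. The second overlooks the blinding measures. The third holds only near a true difference of 6 points; the rate runs from about 80% down to 6% as the true difference rises from 3.33 to 10 points. Nor can one quote a rate at which this plan would rank identical shams falsely, because that requires a set of unadjusted pairwise tests, a ranking rule and an effect size that the protocol does not state.

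The reply does not remove the mismatch. An analysis plan could add a margin, but it could not make 30 to 35 patients per arm precise enough for the word determine. And neither efficacy nor blinding is linked to a criterion for choosing a sham.

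**Conclusion.** The point holds in limited form. The protocol promises to determine the optimal sham without saying what makes one optimal. So far as the answer turns on a sham's own activity, the planned difference tests cannot supply it at this arm size. The size of the problem depends on the true difference, and only the 3.33-point figure comes from the protocol; 0.5 SD, 8 and 10 points are benchmarks, because the document states no NPQ margin. The calculations assume two-sided 0.05, a common SD of 11.87 and a complete-case n of 30 to 35. The finding is that a non-significant sham comparison would be uninformative, not that the sponsor intends to misread one.

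**What to change.** - **Statistical analysis:** estimate B−E, C−E and D−E in NPQ change from one model over all five arms, with confidence intervals, and report them alongside the Blinding Index. Say how activity and blinding together bear on what optimal means.
- **Same section:** state that P above 0.05 will not be read as inert or equivalent, and that shams will not be ranked by which comparison with group A is significant. Call a sham equivalent to group E only if its whole 90% CI lies within a margin that the sponsor fixes, with its reason, before unblinding. Otherwise report the comparison as inconclusive.
- **Aims:** in the abstract, replace the promise to determine the optimal sham with estimating the differences between sham types, labelled exploratory, and align the Background, which already speaks only of investigating.
- **Acupoint specificity:** use A−C for this only after two places are reconciled. The Interventions text says that non-acupoint needles are inserted with no acupuncture technique applied, while Table 1 makes de-qi necessary in group C. Until then the contrast may not isolate location.

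The cost is wording and a few contrasts from a single model, with no added patients or visits. The second aim becomes more modest, and with intervals of about plus or minus 5 points most sham comparisons will probably be inconclusive unless the margin is wide.

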**Trial registration:**

Chinese Clinical Trial Registry: ChiCTR-IOR-15006886. Registered on 2 July 2015.

**Electronic supplementary material:**

The online version of this article (doi:10.1186/s13063-017-2009-1) contains supplementary material, which is available to authorized users.

## Background

Chronic neck pain (CNP) is a serious public health and socioeconomic problem worldwide. Studies have shown that the overall prevalence of CNP varies from 0.4 to 86.8% (mean 23.1%) [1]. The prevalence of CNP is greater among office workers than manual workers. This condition is characterized by activity limitations, dizziness, anxiety and insomnia [2]. Physical exercise, massage or physiotherapy, as well as education, have been proved to be efficient in reducing neck pain [3–6]. Acupuncture has also been well accepted as a non-pharmacological treatment for neck pain [7]. However, the treatment effect of acupuncture is moderate [8]. One argument is that “acupuncture is not associated with clinical effects beyond a powerful placebo response” [9, 10].

A growing body of research indicates that clinical trials of acupuncture have encountered many methodological challenges, including the identification of appropriate treatment and control groups, deficiencies in the blinding and follow-up of chronic pain [11]. Firstly, variable acupoints at different sites are commonly selected for the same disease in clinical practice. Based on our clinical experience, more than 20 acupoints have been selected as the main acupoints in neck pain. An appropriate repeatable treatment has not been established. Secondly, although shallow needle insertion and non-acupoints have been widely used in acupuncture research in sham groups, it has been suggested that these methods have therapeutic effects and are adjusted to accommodate different patients according to traditional Chinese medicine (TCM) theory [12]. The academic literature also indicates that the human body has more than 2200 singular points within formal naming beyond meridians [12]. The notion of a non-acupoint is obscure and there may be a role for specific factors of non-acupoints lateral to the acupoints [13]. Moreover, recent academic literature has shown that shallow puncture also produces analgesic effects in pain disorders. Thirdly, it has been reported that about 40% of subjects in these trials could distinguish non-penetrating sham acupuncture from real acupuncture [14].

In view of these doubts, the influence of different needling points and depths should be investigated. First, the acupoints of local lesions including *Jingbailao* (EX-HN 15) and *Jianzhongshu* (SI 15) are commonly used in our hospital for neck pain [15]. The analgesic mechanism of acupoints on local lesions has been established in the spinal segments control theory to explain the gate control theory [16, 17]. According to the innervations of the pain focus, the effects of stimulation of EX-HN 15 and SI 15 on neck analgesia will be studied for feasibility and repeatability [15]. Second, several different groups of non-acupoints and shallow punctures will be established to determine whether traditional acupuncture is more effective for chronic pain relief than sham acupuncture in adults with CNP. The different depth and placement of needle insertion will also be investigated to determine efficacy [18]. Third, a single-blinded practice will be used and the adequacy of subject blinding will also be carefully assessed. The patients will be advised to lie in the prone position on the treatment couch and will be unaware of the treatment course in this trial. Data collection will be completed by the researchers over a 3-month follow-up period. Finally, we will assess the pain threshold (PT) and pain diary as semi-objective outcomes to avoid subjective results.

In this research, a randomized clinical trial will be performed to determine whether the outcome of traditional acupuncture treatment is significantly different to sham acupuncture in relieving CNP. We also aim to investigate which type of sham acupuncture is the optimal control for clinical trials.

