Group B acupoints shallow puncture	EX-HN 15 (*Jingbailao*)	The needles are pierced through the skin for 0.2 cun and not enough to produce *de-qi*
	SI 15 (*Jianzhongshu*)	
Group C non-acupoint acupuncture	Non-acupoint 1	The needle-punching depth in the acupoints is 0.5 to 0.8 cun. The sensation (denominated *de-qi*) is necessary
	Non-acupoint 2	
Group D non-acupoint shallow puncture	Non-acupoint 1	The needles are pierced through the skin for 0.2 cun and not enough to produce *de-qi*
	Non-acupoint 2	
Group E sham puncture	EX-HN 15 (*Jingbailao*)	The placebo needle tip is pressed and fixed on the skin of the acupoint
	SI 15 (*Jianzhongshu*)	

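### Needling point and depth are stated questions and arms A to D cross them in a 2x2 layout, but the article names no point, depth or interaction effect

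*Protocol article*

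**What the plan says.** **Questions.** The Background states "In view of these doubts, the influence of different needling points and depths should be investigated" and later "The different depth and placement of needle insertion will also be investigated to determine efficacy". The Discussion says that the trial is meant "to determine the evidence for the specificity of acupoints". These stand beside two other aims: whether traditional acupuncture beats sham, and the choice among shams ("We also aim to investigate which type of sham acupuncture is the optimal control for clinical trials").

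**Arms.** Table 1 in Interventions gives:

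| | Deep (0.5 to 0.8 cun), de-qi required | Shallow (0.2 cun), no de-qi |
|---|---|---|
| Acupoint | A | B |
| Non-acupoint, 1 cm lateral | C | D |

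For group C the entry reads "The needle-punching depth in the acupoints is 0.5 to 0.8 cun. The sensation (denominated *de-qi*) is necessary". For B and D it reads "The needles are pierced through the skin for 0.2 cun and not enough to produce" de-qi. Group E, the blunt needle on the acupoints, lies outside this layout.

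**Sizing and analysis.** The sample size section gives one pilot mean to the treatment arm and the other to all four controls. The Statistical analysis section says "Group differences for continuous variables will be analyzed using analysis of variance (ANOVA"). Neither section mentions a point effect, a depth effect, an interaction or a contrast.

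**The concern.** The stated analysis does not match part of the stated purpose. A five-group F test asks whether any arm differs from any other. A significant result does not say whether site or depth is responsible, and a non-significant one gives no interval for either. The arms needed for those questions are already in the trial, so the information will be collected whether or not it is summarised.

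At stake is how claims about acupoint specificity and depth will be supported. If no effect is named in advance, the comparison that stands for specificity (A against C, B against D, or the two acupoint arms against the two non-acupoint arms) can be chosen after the five means are seen. These comparisons differ in precision and, if site and depth interact, in what they estimate.

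**Working it through.** **Inputs (Sample size calculation section).** Pilot NPQ changes are 20.71 (SD 11.91) and 24.04 (SD 11.83). The minimum is 30 per arm, with 35 recruited. Power is 90% and alpha 0.05. Sidedness is not stated, so two-sided is assumed, with a common SD in all arms.

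- Pooled SD = √[(11.91² + 11.83²)/2] = 11.87
- Difference = 24.04 − 20.71 = 3.33 (only its size matters here)

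**The plan's own figure.** For two means, n = 2 × (1.960 + 1.282)² × 11.87² / 3.33² = 267.02, so 268 per arm. One-sided it is 218. A five-group ANOVA with one arm different needs 246. The stated 30 is not reproduced. At 30 per arm, power is 19% for a pair and 16% for the ANOVA. That is a separate and larger problem, noted because it limits what any analysis of these arms can deliver.

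**Precision of each kind of contrast.** With n per arm:

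| Contrast | SE | n = 30 | n = 35 | 95% CI half-width, n = 30 | Detectable with 90% power, n = 30 |
|---|---|---|---|---|---|
| Simple effect, e.g. A − C | SD√(2/n) | 3.06 | 2.84 | 6.0 | 9.9 |
| Main effect, e.g. (A+B)/2 − (C+D)/2 | SD√(1/n) | 2.17 | 2.01 | 4.25 | 7.0 |
| Interaction, (A−B) − (C−D) | SD√(4/n) | 4.33 | 4.01 | 8.5 | 14.0 |

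The half-width is 1.96 × SE and the detectable difference is 3.242 × SE. The ratio of simple-effect to main-effect variance is (2/n)/(1/n) = 2.

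**Pattern 1: no interaction.** The simple and main effects estimate the same quantity.

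- Effect 3.33: power is 19% for a simple effect and 34% for the main effect at 30 per arm (22% and 38% at 35).
- Effect 7: 63% and 90% at 30 per arm.
- For 3.33 points, 90% power on a main effect would need 267.02/2 = 133.51, so 134 per arm.

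**Pattern 2: only A differs, by d.** This is the pattern in the sample size section, with B, C and D equal. Then A − B = d and C − D = 0, so each main effect is d/2 and the interaction is d.

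- d = 3.33: A v B or A v C has 3.33/3.06 = 1.09 standard errors and 19% power. A main effect has 1.67/2.17 = 0.77 and about 12%. The interaction has 3.33/4.33 = 0.77, so the same 12%.
- d = 10: 90% for A v B and 64% for the main effect.

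So pooling gains under the first pattern and loses under the second, and the interaction test is too imprecise to tell them apart reliably.

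**Whether the layout is clean.** Table 1 changes depth and de-qi together, so the second factor is deep needling with de-qi against shallow needling without it. The Interventions text also says that needles at non-acupoints are placed without acupuncture technique, while Table 1 makes de-qi necessary in group C. If the text governs, the deep level is not the same in A and C.

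**The case against.** Four points can be made on the other side.

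1. **Nothing excludes the contrasts.** Point, depth and interaction effects are linear contrasts of the same arm means with the same residual variance as the ANOVA. The article is condensed, and an analysis plan that is not shown may name them. This stands against any inference that the trial will end with no estimate of point or depth. It does not remove the mismatch in the article, which states these questions and then describes sizing and analysis only by group.

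2. **B, C and D are there as shams.** The Background introduces the non-acupoint and shallow arms to test traditional against sham needling, and choosing among shams needs arm-level comparisons. This stands: a reader should not infer that the component questions are the only reason for those arms, or that a factorial analysis could replace the arm-level ones.

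3. **The efficiency gain is conditional.** A reader might infer that factorial main effects halve the variance at no cost. The sample size section assumes the pattern under which they lose power. This stands, and it is why main effects cannot be the sole or leading summary. Equally, A-only cannot be presumed: the Background and Discussion both say that shallow and non-acupoint needling may have effects of their own.

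4. **Little power is gained.** Even without interaction, power for 3.33 points is only 34% to 38%. This stands too. The case for the change is a defined estimate with an interval, not adequate power.

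**Conclusion.** The point holds in a limited form. The protocol raises point, depth and acupoint specificity as questions and lays out arms A to D so that they could be addressed, but the article's sizing and analysis treat the arms only as separate groups and name no matching effect. It is worth correcting because the remedy uses data already being collected.

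At SD 11.87 and 30 per arm, the standard errors are 3.06 (simple effect), 2.17 (main effect) and 4.33 (interaction). The main effect's advantage depends on no interaction between point and depth. Under the A-only pattern it is diluted to half and the simple comparisons with A are stronger. All of this takes Table 1 as the description of the arms and assumes a common SD equal to the pilot's. The documents do not support saying that these effects can never be estimated, or that half the information is necessarily lost.

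**What to change.** Add one paragraph to Statistical analysis, as a pre-specified secondary analysis of NPQ change in arms A to D. Report each of the following with a 95% confidence interval:

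- the simple effects: A v B, C v D, A v C and B v D;
- the point-by-depth interaction;
- the two main effects: point (A+B v C+D) and depth (A+C v B+D).

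Label the second factor deep with de-qi v shallow without. Keep arm E outside. State that the main effects are not to be read without the simple effects and the interaction, and that a non-significant interaction does not show its absence, given its standard error of 4.33. Leave the A-versus-sham and between-sham comparisons as they are.

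Before the factorial is interpreted, reconcile the Interventions text with Table 1 on needling technique at non-acupoints.

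The cost is a paragraph of text and a longer results table. Arms, patients and visits do not change. The shortfall in power for the 3.33-point pilot difference remains and needs its own remedy.
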